##### Implementation Outcome Indicators

Implementation outcomes are defined by Proctor et al as “the effects of deliberate and purposive actions to implement new treatments, practice, and services” [41]. A total of 5 implementation outcomes were selected as quantitative indicators and are presented in Table 2. These data will be obtained from the hospital’s EMR, the Medly system’s audit trails, and technical support logs.

##### Semistructured Interviews With Program Staff

Separate semistructured interview guides based on the constructs in the CFIR will be formulated for each category of program staff previously outlined. Interviews will be conducted at baseline, 4 months, and 12 months to align with the different phases of Stetler et al’s typology of formative evaluations [43]. The interviews are expected to last approximately 30 min and will be conducted at a location convenient to the participants. All interviews will be audiotaped for later transcription and analysis.

##### Planned Analyses

Descriptive statistics will be produced for the indicators of the implementation outcome to provide an objective measure of implementation success.

Furthermore, 2 independent researchers will analyze interview transcripts and documents using the Framework Method of qualitative analysis [44]. An initial round of coding will use a deductive approach by looking for themes that match the constructs in the CFIR. A second round of coding will be inductive using an open coding approach, which will involve researchers looking for unexpected themes that are not represented in the guiding CFIR framework. Throughout the analysis, both reviewers will discuss the themes and codes from their independent analyses to come up with a single analytical framework. This finalized framework will be applied in a final coding of all transcriptions using NVivo (QSR International, Doncaster, Victoria, Australia) [45].

Quantitative and qualitative data will be triangulated such that the interview data will help explain success or failure of the implementation.

#### Objective 3: Describing Patient Adherence and Usage Patterns

A sequential explanatory mixed-methods approach [46] will be used consisting of a quantitative measurement of patient adherence and semistructured interviews with patients at 4 time points.

##### Patient Adherence

Adherence will be assessed by analyzing patient usage rates of the Medly system—specifically, the proportion of days for which the patient took a complete reading (weight, blood pressure, and symptoms) over the previous 30 days. Usage data will be obtained and exported on a regular basis through Google Analytics [47].

##### Semistructured Interviews

A sample of patients enrolled in the Medly Program will participate in semistructured interviews aimed at understanding reasons for adherence or nonadherence and their general experiences with the Medly Program. Interview guides will be formulated based on the constructs of the Unified Theory of Acceptance and Use of Technology 2 [48]. For example, we will explore how patients’ expectations, ease of use of the intervention, facilitating conditions (eg, quality of technical support services), and the direct or indirect influence of clinicians and loved ones could explain levels of uptake, adherence, and use. Unlike adherence, which will be calculated for all patients enrolled in the Medly Program, interviews will be conducted until information saturation is reached using maximum variation sampling [49] based on age, sex, experience with technology, health status, time since enrollment, and level of adherence. As recommended by Francis et al for theory-based interview studies, an a priori target of 10 patients is being set as the initial analysis sample [50]; however, interviews will continue until no new themes emerge [50]. For patients who withdraw from the Medly Program before the end of the evaluation period, reasons for this withdrawal will be documented as part of standardized off-boarding procedures and a sample will be asked to participate in an interview. The interviews are expected to last 20 to 30 min and will be conducted in a quiet and private space within the clinic (eg, consultation room) during a regular clinic visit or over the telephone. All interviews will be audiotaped and transcribed for later analysis.

##### Planned Analyses

Monthly adherence rates will be examined using descriptive statistics to identify any patterns in the increase or decrease of patient adherence to Medly over time. In addition, general linear mixed model procedures will be performed to determine if any baseline patient characteristics (eg, age, sex, and HF severity) or time since program enrollment predicts patient adherence to the Medly system. Semistructured interviews will be analyzed using the Framework Method [44], as previously described.

#### Objective 4: Cost Impact of Implementing the Medly Program

The costs associated with implementing the Medly Program will be determined from the perspectives of the public payer, hospital, and patient. In reporting these results, costs will be interpreted in relation to the patient-level impacts determined in objective 1.

##### Data Acquisition

Costs will be calculated using a 6-month time frame. Specifically, we will compare costs before the implementation of the Medly Program (assessed at baseline) versus the costs after enrollment of patients into the program (measured at 6 months). This time frame was chosen because it represents the time horizon over which most of the health effects and costs of using the Medly Program are expected. Most of the cost variables will be self-reported by patients and triangulated using administrative data whenever possible (eg, EMR data). Therefore, questions related to the cost will be added to the patient outcome questionnaires (objective 1) and will be administered at baseline and 6 months.

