##### Data Acquisition

Data collection will occur at baseline, 1 month, 6 months, 12 months, and 24 months, or until the patient exits the program. Data collected in addition to the primary evaluation period (baseline to 6 months) will provide an opportunity for post-hoc analyses aimed at quality improvement, including recommended duration of use. For example, the 1-month time point was included to determine if the bulk of changes to self-care and QoL occur immediately after enrollment. Similarly, longitudinal data will help determine whether patient-level impacts are sustained or change when using the system long term.

Health service utilization, laboratory results, mortality, prediction of survival, and select demographic information will be obtained from the hospital EMR. In addition, health service utilization information will be verified by patient participants through self-reports via a questionnaire.

Baseline and follow-up questionnaires containing the validated survey tools listed in Table 1 will be distributed to patients during regularly scheduled visits. Upon study enrollment, patients will be asked whether they prefer to be mailed the questionnaire or completing it using an online survey tool (SurveyMonkey [38]) in the event that they do not have a clinic visit scheduled for the data collection time point. In these situations, the questionnaires will be sent to the patient according to the preferred format and they will be given 2 weeks to respond, after which a member of the evaluation team will call the patient to remind them to complete the questionnaire.

**Table 1 table1:** Timing of outcome assessments for the impact evaluation.

Domain and measure		Baseline	1 month	6 months	12 months	24 months	Exit

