##### Power Consideration

We will aim to recruit at least 108 patients into the Medly Program at the HF clinic before analyses of patient-level outcomes are undertaken. This number is based on being able to detect a small effect size (Cohen *d*=0.3) in the number of hospitalizations because of HF within the first 6 months of enrollment with 80% power and an alpha of .05 (two-sided) [40]. This number considers that approximately 20% of patients will be “lost to follow-up,” which includes patient mortality and those who withdraw from the program before the 6-month time point. We anticipate recruiting this number in the first 18 months of the program.

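### Self-reported cost questions are scheduled at baseline and 6 months but not at program exit, so patients who leave early have no scheduled self-reported post-enrollment cost

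*Protocol article*

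**What the plan says.** The Data Acquisition section under Objective 4 sets the cost window: "Costs will be calculated using a 6-month time frame". It compares cost before the program, assessed at baseline, with cost after enrollment, measured at 6 months. On the source it says "Most of the cost variables will be self-reported by patients", with administrative data used for triangulation where possible. On timing it says "questions related to the cost will be added to the patient outcome questionnaires (objective 1) and will be administered at baseline and 6 months".

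The Data Acquisition section under Objective 1 has a wider schedule: "Data collection will occur at baseline, 1 month, 6 months, 12 months, and 24 months, or until the patient exits the program". Table 1 has an Exit column. It is marked for the utilization counts (hospitalizations, hospital days, emergency visits, HF outpatient visits, family doctor visits, medication changes), for the dyspnea scale, and for the SCHFI, EQ-5D-5L and MLHFQ.

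The Power Consideration section allows for "approximately 20% of patients will be “lost to follow-up,” which includes patient mortality and those who withdraw from the program before the 6-month time point".

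**The concern.** The cost items are attached to the Objective 1 questionnaires, but they follow a shorter schedule than those questionnaires. A patient who leaves at month 3 would complete an exit questionnaire without the cost items. Because data collection runs only until exit, nothing in the article provides for asking that patient again at month 6. The same patient's baseline cost has been collected.

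This gap arises at data collection. An analysis plan can choose how to handle missing values, but it cannot recover answers that were never requested. Early loss includes deaths, and the Patients section leaves the duration of participation to the patient and cardiologist, so those without a post-enrollment answer may differ from those who stay. Cost is one of four stated objectives, and its results are to be read alongside the impact results.

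**Working it through.** **1. The plan's own figure.** For a paired comparison with d = 0.3, two-sided alpha .05 and 80% power, the normal approximation gives ((1.960 + 0.842)/0.3)² = 87.2, so 88 patients. The noncentral t gives 90 (power 0.804). Allowing for 20% loss, 88/0.8 = 110 and 90 × 1.2 = 108, so the stated 108 is reproduced to within 2 (90/0.8 would give 113). The 20% loss is thus already inside the 108.

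**2. How many patients are affected.** 0.20 × 108 = 21.6, about 22 patients, leaving about 86 with a scheduled 6-month cost questionnaire. Applied to the 166 enrolled by April 2018 (Results), 0.20 × 166 = 33.2, about 33. The split between deaths and withdrawals is not given.

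**3. Which costs are affected.** Each perspective is set against the sources that remain for an early leaver.

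| Perspective | Still available | Not scheduled |
|---|---|---|
| Public payer | Hospitalizations, emergency, HF clinic and family doctor visits (medical record; Table 1, Exit) | Probably home care, which is not in Table 1 |
| Hospital | Staff time, kit, data plan, server, analyst salary | Little or nothing from the patient questionnaire |
| Patient | Program-use time in part, from audit trails, support logs and usage data | Travel and appointment time, missed work, out-of-pocket costs, caregiver time |

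The article does not say how far the hospital record captures care given elsewhere, so the payer cover may be incomplete.

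**4. What this could do to the before/after change.** Take one self-reported component. Let f be the fraction with no post-enrollment value and g the leavers' mean change minus the stayers' mean change, in units of the mean baseline cost of that component. The full-cohort change is (1 − f) × stayers' change + f × leavers' change, so a stayers-only change differs from it by −f × g. The documents give no value for g; the values below are assumptions, with f = 0.20.

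| Assumed g | Stayers-only minus full-cohort change |
|---|---|
| −0.5 | +0.10 |
| 0 | 0 |
| +0.5 | −0.10 |
| +1 | −0.20 |
| +2 | −0.40 |

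A negative result makes the program look cheaper, a positive one dearer. At f = 0.10 each figure halves. The sign follows g alone.

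**5. Why the period must be recorded.** As an illustration, suppose a patient costs a constant c per month and leaves alive at month 3. The before period gives 6c and the exit form gives 3c. The apparent change is −3c, a fall of 50%, although the monthly cost has not changed. Adding exit items without a rule for observation time would replace one problem with another.

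**The case against.** The strongest reply is that much of the cost of early leavers is collected anyway. Utilization comes from the hospital record and is counted at exit, hospital costs are staff time and equipment, and system logs can partly approximate time spent using the program. This stands. A reader might infer that leavers supply no post-enrollment cost at all; the documents do not support that, and a final admission, for example, would usually be captured.

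A reader might also infer that the comparison is biased towards savings. That is plausible if leavers become costlier, but it is not shown. Someone who leaves early has less time in which to accrue travel, appointments and system use. Exit may also be agreed for reasons other than deterioration.

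Third, an exit questionnaire cannot be completed by patients who die. This also stands and limits what the change can recover.

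Finally, denominators, partial observation and sensitivity analyses are usually settled in a full protocol or analysis plan, which is not shown. That is fair for the analysis. The article does not say that baseline values of all patients will be set against 6-month values of the remainder, and its planned tests for patient-level outcomes are paired. The reply does not reach the collection schedule, which the article itself fixes.

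**Conclusion.** The point holds for self-reported costs. On the stated schedule, about 20% of patients (about 22 of 108) would have no scheduled self-reported cost after enrollment, although an exit questionnaire already exists for those who leave alive. The patient perspective is mainly affected, with home care a probable gap in the payer perspective. The primary outcome is not touched.

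The consequence is a risk of selective missingness whose direction and size cannot be stated. The count of 22 rests on the protocol's own loss assumption; any bias figure would rest on a leaver/stayer cost difference that the documents do not give. This is an inexpensive improvement to one of the four objectives and does not invalidate the cost analysis.

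**What to change.** In the Data Acquisition section under Objective 4, schedule the cost items at enrollment, at month 6 and, for anyone leaving sooner, at program exit on the questionnaire that Table 1 already provides. Record the dates the exit answers cover, and state how the shorter period is accounted for against the 6-month before period.

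For patients who die or do not return the exit form, cost the care in the medical record up to death or 6 months, and state that their self-reported items are missing.

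The cost is a slightly longer exit questionnaire and some extra analysis of records already planned for collection. Self-reported costs of patients who die will still be missing.

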###### Public Payer Perspective

Costs to the public payer will be determined by looking at health care utilization of patients enrolled in the Medly Program before versus after their enrollment. These will include hospitalizations, ED visits, HF clinic visits, family physician visits, and use of home care services. In addition, costs for inpatient medications will be considered.

###### Hospital Perspective

Costs from the hospital perspective will be valued based on time spent by human resources involved in the Medly Program. This time will be converted to costs based on those individuals’ respective salaries. This will include time the clinicians spent reviewing and responding to Medly alerts as well as time the clinicians spend in training sessions, learning to use the system, and seeking technical support. In addition, costs for the hospital perspective will include equipment costs (Medly kit, smartphone data plan, and server) and the salary for employing a telehealth analyst responsible for recruiting, training, onboarding, managing inventory support, and providing training.

###### Patient Perspective

Costs for patients will primarily be determined by the time they spend accessing care for HF. This will involve determining their employment status and annual income as well as time they spend traveling to and from appointments, time spent at appointments, and how much work time was missed because of their HF condition (vacation or unpaid). In addition, this will include the time patients spent learning to use the Medly system, time spent using the system, and time getting technical support. Additional costs considered include travel, parking, and all other out-of-pocket costs related to accessing care or using the intervention. Moreover, time of informal caregivers (eg, friend or family member who helps the patient to manage their HF) will be valued as part of the patient perspective. Costs for informal caregivers will be based on the average hourly rate of personal support workers.

## Results

The Medly Program was launched in August 2016. As of April 4, 2018, 166 patients have been enrolled. The primary impact analysis is expected to be conducted by January 2019.

## Discussion

This study aims to evaluate the implementation and impact of a smartphone-based TM program being implemented as part of the standard of care in a specialty care setting in a large Canadian city.

### Limitations

Unlike TM systems evaluated in the context of academic research, the lack of strict patient inclusion and exclusion criteria for the Medly Program has the potential to lead to heterogeneity among evaluation participants, which will make it difficult to generalize the results to other health care settings. Another important limitation is that the nature of this evaluation and the availability of data do not allow for a distinct comparator group. Without discounting these limitations, we believe that one of the strengths of this evaluation is its pragmatic nature and that these threats to internal and external validity will be mitigated through a detailed description of the context and participants when results are reported. The interpretation of the Medly Program evaluation results will include comparisons with previous TM RCTs conducted within the HF clinic [30] and other comparable settings, as well as other RCTs evaluating interventions designed to promote self-care through education and health coaching conducted within the HF clinic [51]. This is possible because of the selection of outcome metrics common in other TM studies.

### Conclusions

Unlike other TM studies that focus primarily on quantitative outcomes, this evaluation will also examine the context and mechanisms that lead to them. Therefore, this pragmatic mixed-methods study will allow for an interpretation of results using realist evaluation principles [52]. The information gathered during this evaluation will inform if, and how, a smartphone-based TM system improves the self-care capacities, clinical management, and health outcomes of patients with HF. This evaluation will lead to quality improvement of the current program and provide evidence that will inform the implementation and sustainability of other TM programs.

## Abbreviations

BNP: brain natriuretic peptide
CFIR: Consolidated Framework for Implementation Research
ED: emergency department
EMR: electronic medical record
EQ-5D-5L: EuroQol five-dimensional
HF: heart failure
LVEF: left ventricular ejection fraction
MLHFQ: Minnesota Living with Heart Failure Questionnaire
QoL: quality of life
RCTs: randomized controlled trials
SCHFI: Self-Care of Heart Failure Index
SHFM: Seattle Heart Failure Model
TM: telemonitoring
